## Abstract

**Background:**

Malnutrition is a recurring problem that has become more relevant in recent years. The aim of this study is to assess the risk of malnutrition and nutritional status on admission and its evolution until discharge in patients aged 65 and over admitted to medical and surgical hospitalization units in hospitals of the Spanish National Health System.

**Methods:**

Prospective observational study to be carried out in the medical-surgical hospitalization units of 9 public hospitals between 01/09/2022 and 31/12/2024. Using consecutive sampling, a total of 4077 patients will be included (453 in each hospital). Variables included are related to the care process, functionality, cognition and comorbidity, risk profile, nutritional status and dysphagia; as well as frailty, dietary quality and contextual variables. The incidence of risk of malnutrition, undernutrition and dysphagia during the care process and at discharge will be calculated. The association with risk factors will be studied with logistic regression models and multivariate Cox regression models. In addition, an analysis of participants’ satisfaction with food services will be carried out. The study was approved by the Ethics and Research Committee on 30/09/2020, approved for funding on 02/12/2021 and with registration number RBR-5jnbyhk in the Brazilian clinical trials database (ReBEC) for observational studies.

**Discussion:**

Some studies address nutritional status or dysphagia in older people in various care settings. However, there is a lack of large sample studies including both processes of the impact of hospitalization. The results of the project will provide information on the incidence and prevalence of both pathologies in the study subjects, their associated factors and their relationship with the average length of stay, mortality and early readmission. In addition, early detection of a problem such as malnutrition related to the disease and/or dysphagia during a hospital stay will favor the action of professionals to resolve both pathologies and improve the health status of patients.

## Introduction

Malnutrition is a recurring problem that has become more relevant in recent years and people aged 65 years and older are common at all levels of health care. Moreover, malnutrition can be aggravated by the presence of diseases and problems such as dysphagia [1]. In particular, assessment and monitoring of nutritional status and dysphagia during hospitalization processes are crucial to provide the highest quality care to avoid undesirable outcomes such as susceptibility to infection, morbidity, and mortality and increased premature readmissions, as well as longer length of stay [2].

Malnutrition is the result of a deficit in the intake or assimilation of nutrients that alters body composition, leading to a decrease in physical and mental capacities, which hinders recovery during an illness process [3]. In Europe, this problem affects approximately 30 million people and costs approximately 170 billion euros per year [4]. Disease-related undernutrition, on the other hand, is caused by inadequate nutrient and energy intake about nutritional requirements in a situation where disability and disease are at the core of the problem. This type of malnutrition is due to the bodily changes and loss of functionality that occur when there is an acute or chronic illness [5]. Furthermore, different studies show that the nutritional status of patients worsens during hospitalization [1], increasing morbidity and mortality, hospital stay, and costs for the healthcare system [6,7].

People aged 65 years and older are particularly susceptible to undernutrition and disease-related undernutrition. This is due to physiological changes during ageing, the presence of associated diseases, and the specific nutritional needs of this population (decreased activity, alterations associated with swallowing disorders or frailty, among others) [8,9]. In this regard, international studies estimate that between 35–65% of older people in hospital settings are undernourished [10,11].

In Spain, the prevalence of undernutrition in people over 65 years of age is around 10%, with a risk prevalence of 23.3% [12]. In the hospital setting, the PREDYCES (Prevalence and costs of malnutrition in hospitalized patients) study established a prevalence of disease-related undernutrition of 23.7% in the general population, increasing to 37% in patients over 70 years of age [5]. Recent studies establish a prevalence of disease-related malnutrition on admission to inpatient units of 26.9% and, in addition, 18% of patients develop malnutrition during hospital stay [13]. Some authors point to an under-diagnosis of this problem, possibly related to the lack of standards in the detection and screening of malnutrition risk [13]. For these reasons, it is estimated that at least one in three patients over 65 years of age admitted to the hospital is malnourished, with an additional cost of between €1,400–1,800 for each hospital admission of a patient at risk of disease-related malnutrition [5,14].

On the other hand, oropharyngeal dysphagia is defined as the difficulty or inability to swallow solid, semi-solid, or liquid food from the oral cavity to the stomach [3]. Dysphagia is a symptom that accompanies other diseases and can affect up to 30–40% of the population over 65 years of age and up to 44% of elderly people admitted to hospital. It is estimated that, in Europe, 80% of patients are neither diagnosed nor receive any treatment for this pathology [15]. Furthermore, dysphagia is associated with a higher prevalence of malnutrition, along with other conditions such as frailty [16], neurological diseases, or neoplasms [17]. Some studies establish a joint prevalence of undernutrition and dysphagia ranging from 3–29% [18]. However, no international studies addressing both problems together in the hospital setting were retrieved.

Some factors that may explain the high rates of disease-related malnutrition and dysphagia are the lack of means and the scarcity of information on nutrition by professionals [13], as well as the quality of the food offered in hospitals [19]. The level of acceptance of hospital food has an important relationship with the user’s overall satisfaction and quality of life during admission [20]. Thus, the assessment of the quality of menus during hospital admission and patient satisfaction is considered an appropriate method of nutritional assessment in patients at risk of malnutrition and dysphagia [21].

Disease-related malnutrition and dysphagia are associated with increased hospital morbidity and mortality, length of stay, readmission rates, and associated costs [22]. Nutritional screening, early detection, and monitoring of nutritional status and dysphagia should be a fundamental part of the care plan for patients, especially in patients aged 65 years and older in inpatient units [6,7]. However, research currently places insufficient emphasis on the coexistence of malnutrition and dysphagia at the hospital level. Indeed, in Spain, some studies address the nutritional status of people aged 65 years and older in various care settings, using different definitions and screening tools [1,4,16]. Despite this fact, there is a lack of national studies on the joint prevalence of malnutrition and dysphagia conducted on a large sample of patients and including an assessment of the risk factors associated with both processes, as well as their evolution and consequences during hospitalization.

Therefore, this project will study the evolution of nutritional status and dysphagia in patients aged 65 and over during the care process in medical and surgical hospitalization units in Spanish hospitals. In addition, sociodemographic, clinical, functional status, frailty, and healthcare context-related characteristics that may be associated with the presence of malnutrition and dysphagia will be identified. Finally, patient satisfaction with food services in the participating centers will be studied.

## Materials and methods

### Research hypothesis

The nutritional status of patients aged 65 years and over admitted to the medical and surgical inpatient units of the participating hospitals evolves unfavourably from admission to discharge and may increase the length of stay, hospital mortality, and early readmission.

### Aims

The main objective of this project is to assess the risk of malnutrition and nutritional status on admission and its evolution until discharge, in patients aged 65 and over admitted to medical and surgical units in hospitals of the Spanish National Health System. In addition, the aim is to respond to the following specific objectives:

To identify the incidence and prevalence of risk of malnutrition and the presence of malnutrition and associated factors on patient admission and discharge.To describe the evolution of nutritional status during patient hospitalization.To analyze the average length of stay, hospital mortality, and early readmission as a function of nutritional status at admission and the presence of dysphagia in the study cohort.To determine the incidence and prevalence of dysphagia and associated factors on admission and discharge.To determine satisfaction with the quality of patient nutrition at discharge, the type of hospital food service, and the characteristics of the hospital nutrition unit.

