### Sample/Participants

The study population consists of the users of the medical and surgical inpatient units of the participating hospitals. Participants will be selected through consecutive case sampling.

The study will include patients aged 65 years or older who are admitted to the inpatient units, with an expected stay of at least 48h and who sign the informed consent form (or their legal guardian). Patients admitted with enteral nutrition or parenteral nutrition, terminally ill patients, patients with a primary diagnosis of cancer, patients admitted to critical care units, and with a diagnosis of COVID-19 illness at admission or during the stay will be excluded. Withdrawal criteria during follow-up will include: i) patients transferred to another hospital or unit not participating in the study; ii) any patient meeting any exclusion criteria at any time.

To calculate the sample size, the Freeman criterion for multivariate logistic regression analysis in epidemiological studies was considered first [23]. Taking into account that a maximum of 20 independent variables (k) will be included in the model at the same time and that it is intended to carry out both a global analysis and an analysis by a hospital, an initial sample size of n = 10*(k+1) = 10*(20+1) = 210 patients per hospital is estimated and, estimating possible losses of 15%, a total of 242 patients per hospital will be necessary. Secondly, given that we intend to study the prevalence of malnutrition and/or dysphagia in each of the participating hospitals and that in the literature the prevalence of malnutrition and/or dysphagia presents great variability, it seems appropriate to consider a prevalence of 50% (will guarantee the necessary sample size) which, for the confidence of 95%, a precision of 5% and a percentage of losses of 15%, will require a sample size per hospital of 453 patients (GRANMO-IMIM sample size calculator). Therefore, the total sample will be 4077 participants, and a recruitment and follow-up period of 18 months is estimated to be necessary.

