#### Phase 3: Situation on discharge

In addition to the variables indicated, on the day of discharge from the hospital, the daily intake record book will be collected and the food satisfaction survey will be provided. The variables related to the care process (days of stay, hospital mortality, and whether it was early readmission) will also be recorded.

Finally, the patient will be given the continuity of care report at discharge, drawn up by the responsible physician together with the nursing recommendations and information sheets on care related to malnutrition or dysphagia, as appropriate.

Data collection will be carried out electronically through Research Electronic Data Capture (REDCap) (www.prooject-redcap.org) [25,26]. This is a web application that allows the creation of electronic data notebooks for research projects and their online and offline collection from computers and other mobile devices. It also includes a scheduling and alarm system to manage data collection during monitoring. In this regard, it should be noted that the researchers who take on the data collection will receive training on the operation of REDCap and that a pilot of the process of recruiting participants and data collection will be carried out for one month.

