### Data analysis

A descriptive analysis of all the study variables will be carried out, using the appropriate measures according to the type of variable and their corresponding 95% CIs. Firstly, depending on the groups to be compared and compliance with the application requirements, a bivariate analysis will be performed, including the chi-squared or Fisher’s exact test (qualitative variables) and Student’s t-test, ANOVA, Mann-Whitney U-test, or Kruskal-Wallis (quantitative variables), depending on the application conditions.

For the analysis of the evolution of the risk of malnutrition, McNemar’s test or Cochran’s Q test will be used for qualitative variables and paired t-test or Friedman’s rank test for quantitative variables. The incidence of risk of malnutrition and undernutrition will be calculated, as for dysphagia, during the care process and at patient discharge, estimating their corresponding Odds Ratios and 95% CI using logistic regression models.

To assess the possible risk factors for both malnutrition and dysphagia and the socio-demographic and clinical characteristics of the patients, multivariate logistic regression models will be constructed. As independent variables will include: type of nutritional care established according to the risk of malnutrition; daily intake; suspected and diagnosed dysphagia and days of stay. As control variables will include: those related to the risk profile; sociodemographic (sex, age); clinical, functional, cognitive and frailty variables. In the case of mortality and time to readmission, multivariate Cox regression models will be fitted. Independent variables will be included: level of risk of malnutrition at admission; diagnosis of malnutrition at admission; change in risk of malnutrition at admission, at 7 days and at discharge; change in nutritional status at admission, at 7 days and at discharge. Control variables will include: type of nutritional care established (according to risk of malnutrition); daily intake; contextual; related to risk profile; sociodemographic; clinical, functional, cognitive and frailty variables; suspected and diagnosed dysphagia. In all multivariate models, possible interaction effects and possible collinearity will be analyzed.

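### Length of stay is left to ordinary mean or rank tests with no rule separating stays ended by death from live discharges, so it cannot be read as an effect on time to discharge

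*Protocol article*

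**What the plan says.** The Research hypothesis section holds that unfavourable nutritional status "may increase the length of stay, hospital mortality, and early readmission". The Aims section turns this into a specific objective: "To analyze the average length of stay, hospital mortality, and early readmission as a function of nutritional status at admission", and likewise by dysphagia. Under Phase 3: Situation on discharge, stay and death are collected as separate items: "The variables related to the care process (days of stay, hospital mortality, and whether it was early readmission) will also be recorded".

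The Data analysis section then assigns methods. For time-to-event outcomes it says "In the case of mortality and time to readmission, multivariate Cox regression models will be fitted". Days of stay is not among them. It enters a multivariate model only as a predictor of malnutrition or dysphagia, in the list ending "suspected and diagnosed dysphagia and days of stay". The only methods left for days of stay as an outcome are the general ones for quantitative variables: "Student’s t-test, ANOVA, Mann-Whitney U-test, or Kruskal-Wallis (quantitative variables), depending on the application conditions".

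Under Sample/Participants, withdrawals include "patients transferred to another hospital or unit not participating in the study" and any patient who comes to meet an exclusion criterion. The Data analysis section provides multiple imputation for losses to follow-up. The article does not say whether a patient who dies in hospital is included, excluded or reported apart in the length-of-stay comparison.

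**The concern.** Length of stay is itself a time to an event, and the event can be discharge alive or death. A t-test or rank test sees only a number of days. If deaths are kept, a patient who dies on day 3 contributes three days and ranks better than a survivor discharged on day 10. If deaths are dropped, what remains is a selected group, because patients with long stays are exposed to the risk of death for longer and are removed more often.

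This would matter little if mortality were alike across groups. But the hypothesis names hospital mortality as a consequence of poor nutritional status, and the Introduction links both malnutrition and dysphagia to higher mortality. The truncation is therefore expected to be unequal in the very comparison that the objective calls for. A longer time to discharge in malnourished patients could be hidden by early deaths or enlarged by late ones, and the reported difference in days would not show which.

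**Working it through.** **The plan's own figure.** The protocol gives no figure for stay or in-hospital death. Its sample size reproduces: 1.96² × 0.5 × 0.5 / 0.05² = 384.1, rounded up to 385; 385 / 0.85 = 452.9, rounded up to 453 per hospital; 9 × 453 = 4077. Allowing for 15% losses leaves 4077 × 0.85 ≈ 3465 evaluable patients.

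**Inputs.** From the protocol: 3465 evaluable, two-sided 5% level, and 23.7% to 37% malnourished (Introduction). Assumed, because the document is silent: a mean stay *m* of 9 days in the absence of death (range 7 to 12), and in-hospital deaths of 2% v 5%, 3% v 10% or 5% v 15% (others v malnourished).

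**Deaths kept, no real effect on discharge.** Let both groups have the same discharge hazard 1/*m*, with a constant death hazard *h*. The share dying is p = h / (h + 1/m). The mean stay is 1 / (1/m + h) = m(1 − p). The difference (malnourished minus others) is m(p₀ − p₁). For m = 9:

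| Deaths, others v malnourished | Mean, others | Mean, malnourished | Difference (days) |
|---|---|---|---|
| 2% v 5% | 8.82 | 8.55 | −0.27 |
| 3% v 10% | 8.73 | 8.10 | −0.63 |
| 5% v 15% | 8.55 | 7.65 | −0.90 |
| 5% v 5% | 8.55 | 8.55 | 0 |

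Over m = 7 to 12 days and the three unequal pairs, the range is 7 × (−0.03) = −0.21 to 12 × (−0.10) = −1.20 days. The cause-specific hazard ratio for live discharge is 1 throughout.

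**Deaths dropped.** With constant hazards the time of leaving is independent of the reason, so the live-discharge mean is also m(1 − p) and the same differences appear. A simulation with lognormal stays (mean 9 days, coefficient of variation 0.8), exponential death times and the same discharge process in every row gave:

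| Deaths | Mean, all patients | Mean, live discharges |
|---|---|---|
| 2% | 8.85 | 8.89 |
| 3% | 8.78 | 8.83 |
| 5% | 8.64 | 8.72 |
| 10% | 8.27 | 8.44 |
| 15% | 7.90 | 8.17 |

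For 5% v 15% the difference is 7.90 − 8.64 = −0.74 days with deaths kept and 8.17 − 8.72 = −0.55 with deaths dropped. Dropping deaths reduces the problem but does not remove it.

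**Chance of p < 0.05 from mortality alone.** Take the SD equal to the mean. For m = 9, 3% v 10% and 23.7% malnourished, the groups number about 821 and 2644. SE = √(8.73²/2644 + 8.10²/821) = 0.33, and 0.63/0.33 ≈ 1.91, so the chance is about 48%. Across 23.7% to 37% malnourished it is 12–14% (2% v 5%), 48–57% (3% v 10%) and 82–89% (5% v 15%).

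**A real one-day delay.** Suppose the mean time to discharge without death is 10 v 9 days. The observed difference is 10(1 − p₁) − 9(1 − p₀): 9.50 − 8.82 = +0.68; 9.00 − 8.73 = +0.27; 8.50 − 8.55 = −0.05.

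**Timing.** The direction is not fixed. Let live discharges average 10 v 8 days, with deaths of 10% v 3%. If deaths occur on average at day 5, the means are 0.9 × 10 + 0.1 × 5 = 9.50 and 0.97 × 8 + 0.03 × 5 = 7.91, difference 1.59. If at day 15, they are 10.50 and 8.21, difference 2.29. The 2.0-day difference among live discharges shows only which way the all-patient figure moves; it is itself a survivors-only contrast and not a clean benchmark.

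**The case against.** The strongest reply is that this is drawn from silence. A reader might infer that the plan counts deaths as completed stays. The article does not say so: it names an average, records days and mortality separately, and lists general tests. A fuller plan could state how deaths enter. That stands, and the point is not that deaths are known to be miscounted. What remains is that the article assigns methods outcome by outcome, leaves stay out of the time-to-event models, and names tests under which neither keeping nor dropping deaths gives an effect on time to discharge.

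Second, mean days occupied, however the stay ended, is a legitimate measure of bed use, and mortality will be reported beside it. This also stands. If bed use is the target, the shorter mean in a group with more deaths is a true result. It fails only when read as showing whether poor nutritional status delays discharge, a reading that the hypothesis invites by listing longer stay among the harms.

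Third, a reader might infer that transferred patients' stays are also entered as completed. The documents do not support this: such patients are withdrawn, and multiple imputation is planned for losses.

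Fourth, excluding terminally ill patients, primary cancer and critical-care admissions may keep deaths, and so the distortion, small. That is fair, and the size is unknown.

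Finally, hazard or subdistribution ratios do not give average days, which the objective asks for. That is why mean days should stay as a description.

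**Conclusion.** The concern holds in a limited form. As planned, the length-of-stay comparison will move with any mortality difference between groups and cannot by itself support a claim about time to discharge. Rank tests share the weakness, since an early death ranks as a short stay.

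The size is illustrative only. It rests on assumed stays, death rates and death timing. Under equal and constant discharge hazards it runs from about a quarter of a day to about one day, and it is zero when mortality is also equal. No percentage error can be assigned to the trial's eventual estimate, and the direction depends on when deaths occur. The sample size is unaffected. The change is worth making because length of stay is a named consequence in the hypothesis and the remedy is cheap.

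**What to change.** In the Data analysis section:

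1. Keep mean or median days of stay as a descriptive measure of bed use, reported overall and separately for live discharges and in-hospital deaths, by nutritional status and dysphagia.
2. Add an analysis of time to discharge alive with in-hospital death as a competing event: cumulative incidence of live discharge by group, plus a cause-specific or subdistribution model adjusted for admission covariates. Make this the basis for any statement that poor nutritional status or dysphagia prolongs stay.
3. Censor transfers and other withdrawals at the date they leave. State that this assumes non-informative censoring, and check it.

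The cost is a few sentences. Days of stay and hospital mortality are already recorded for each patient, so no new data are needed, provided that the leaving date of withdrawn patients is kept. The small downside is a summary less familiar than a difference in mean days.
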